## Methods/design

### Design of the study

This study is a randomized controlled parallel group intervention trial.

When patients lose equally or more than 5% of their bodyweight in the first 8 weeks of the VLCD, they are included in the intervention trial testing CPI. This arbitrary cut-off value was chosen because of its relatively large effect on the risk profile [3]. Moreover, we need a relevant weight loss to investigate weight maintenance after weight reduction. After randomization, stratified to the achieved weight loss at 8 weeks, participants are assigned to one of the following conditions:

1. VLCD + conventional treatment

2. VLCD + conventional treatment + CPI

The duration of the diet period will be 20 weeks: 8 weeks of VLCD (<800 kcal/day) followed by 12 weeks of slowly reintroducing a normal, mildly energy-restricted diet (1300 kcal/day). During week 10 of the diet, the intervention group starts with a total of 17 sessions of CPI. The first 10 sessions are weekly sessions; followed by two 2-weekly sessions, two monthly sessions, two 3-monthly sessions and 1 session with an interval of 6 months.

Outcome measurements are assessed at baseline, after finishing the intensive CPI-period at 4 months and subsequently at 1 year, 1,5 years and 2 years after randomization. At 8 weeks (randomization after VLCD), only the primary outcome (weight) will be measured.

Figure 1 shows the design of the study.

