### Sample size calculation

After randomization of 75 participants, the sample size calculation was carried out by an independent statistician to base it on realistic data.

Sample size was calculated with SPSS 17.0, using the mixed-model ANOVA procedure described by Aberson [44].

Alpha was set at 0.05, power at 0.80 and the baseline-end correlation at 0.90. A clinically relevant difference between the treatment groups is 5% weight loss [3]. Mean weight at the start of the treatment is about 110 kg, with a standard deviation of 22, this equals an effect size of d = 0.25.[45] With this power calculation we estimate that we need 52 patients in each group. Anticipating a dropout rate of 25%, we aim for a total sample size of 140.

For the most important secondary outcomes we calculated the detectable difference with the sample size of n=104, alpha 0.05 and power 0.80 (Table 2). The detectable differences are quite small, so the aimed sample size seems adequate to analyse at least these secondary outcomes.

**Table 2 T2:** Power calculation secondary outcomes

**Secondary outcome:**	**SD:**	**Detectable difference:(n = 104, β=0.8 α=0.05)**
Waist circumference	11	2.75 cm
Blood pressure sys/dias	20/20	5/5 mmHg
Total cholesterol	1.4	0.35 mmol/l
LDL cholesterol	1.0	0.25 mmol/l
HDL cholesterol	0.7	0.2 mmol/l
Triglyceride	3.0	0.75 mmol/l
HbA1c	12	3 mmol/mol
Insulin	50	12.5 IU
Depression (HADS score 0–21)	3	0.75
Anxiety (HADS score 0–21)	4	1.0
Self esteem (RSE score 10–40)	5	1.25
Fatigue (CIS score 8–56)	13	3.25
Concentration (CIS score 5–35)	8.5	2.1
Motivation (CIS score 4–28)	6	1.5
Activity (CIS score 3–21)	5	1.25
Quality of life (EuroQol 5D score 1–3)	0.5	0.125
Quality of life (EuroQol VAS 1–100)	21	5.25

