### Outcome assessment

Outcome measurements (see below) are assessed at baseline (before start VLCD), and again at 4 months (after VLCD and 10 CPI sessions), 1 year, 1 ½ years and 2 years.

Demographic variables are assessed at baseline by use of a self-administered questionnaire, which is checked during the intake interview with the investigator.

All other secondary outcomes are assessed at baseline, after 4 months, 1 year, 1 ½ years and 2 years, using self-administered questionnaires, except of the Session Rating Scale, which is filled in after every CPI session.

Data are managed by use of the trial management system ‘EXPeRT Clinical’ of OmniComm, USA.

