### Statistical analyses

All analyses will be conducted according to the intention-to-treat as well as the on-treatment principle. We consider participants on-treatment when they miss less then 8 sessions CPI.

At baseline, comparability between the control- and intervention group will be assessed to test the success of the randomization. As measures of central tendency for numerical data we will use the mean (in case of normal distribution) and median values (in case of non-normal distribution), with respectively the standard deviation and interquartile range as measures of dispersion.

Mixed modelling, also known as random effect modelling, multilevel or hierarchical linear regression analyses will be applied for longitudinal analyses of the data. Mixed modelling can efficiently handle data with missing and unbalanced time-points. It corrects for bias when absence of data is dependent on characteristics that are present in the models (missing at random, MAR) [62]. There will be two levels in the models. The patients constitute the upper level, their repeated measures the lower level. First, for each outcome variable a saturated model will be postulated, with the primary or secondary outcomes as dependent variables. The saturated models will include treatment group, time, quadratic time, logarithm of time and all treatment-time interactions as fixed effects. The deviance statistic [63] using restricted maximum likelihood [64] will be applied to determine the covariance structure. Next, using Wald tests, the saturated models will be reduced by eliminating insignificant fixed effects. The significance of the difference between the saturated models and the parsimonious final models will be determined with the deviance statistics using ordinary likelihood.

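### No outcome model fixes baseline adjustment: a free treatment-group term is left to Wald elimination, which can cost precision on weakly correlated secondary outcomes

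*Protocol article*

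**What the plan says.** The Statistical analyses section of the protocol article sets out one modelling route for primary and secondary outcomes alike. The structure has two levels: "The patients constitute the upper level, their repeated measures the lower level". The starting model is stated in full: "The saturated models will include treatment group, time, quadratic time, logarithm of time and all treatment-time interactions as fixed effects". Neither a baseline covariate nor a constraint on the baseline means is listed. The reduction step follows: "Next, using Wald tests, the saturated models will be reduced by eliminating insignificant fixed effects". No term is exempt from it.

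For the secondary outcomes there is a single value before randomisation. Outcome assessment says: "Outcome measurements (see below) are assessed at baseline (before start VLCD), and again at 4 months", with further visits at 1, 1½ and 2 years. Design of the study adds: "At 8 weeks (randomization after VLCD), only the primary outcome (weight) will be measured". Weight therefore has a value at randomisation, while HbA1c, blood pressure, lipids and the questionnaires have only the value from before the diet.

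The sample size was computed "using the mixed-model ANOVA procedure described by Aberson". Its settings were: "Alpha was set at 0.05, power at 0.80 and the baseline-end correlation at 0.90". The Randomization section remarks that weight loss during the diet cannot be corrected for in the analysis because weight is the primary outcome.

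**The concern.** Values taken before randomisation have equal expected means in the two arms. A model that gives each arm its own intercept ignores this. If the effect is then carried by the treatment-time interactions, the baseline enters only through subtraction. For outcomes that correlate strongly over time little is lost. For outcomes that correlate weakly, subtracting a noisy baseline adds variance, and below a correlation of 0.5 the result is less precise than ignoring the baseline altogether.

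At stake are the secondary objectives on glycaemic control, cardiovascular risk and psychological variables. A real effect would be estimated with a wider interval than the data allow. In addition, the reduction rule lets the observed imbalance decide whether the group term stays, so the estimator is not fixed in advance. The remark in the Randomization section suggests that the lack of adjustment may be deliberate. Yet a value taken before allocation can be adjusted for, even when the same variable is the outcome.

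**Working it through.** 1. **The plan's own figure.** Inputs from Sample size calculation: 5% of 110 kg = 5.5 kg, SD 22, so d = 5.5/22 = 0.25; rho 0.90; alpha 0.05 (two-sided assumed); power 0.80. The variance of change in SD units is 2(1-0.90) = 0.20. Per arm, n = 2 × 0.20 × (1.96+0.84)²/0.25² ≈ 50.2, so 51; with the noncentral t, 52 (power 0.806). The stated 52 is thus the group-by-time contrast on change. With baseline adjustment the variance is 1-0.90² = 0.19, which needs 49 per arm; at 52 the power is 0.826. Table 2 follows the same change formula: 0.549 × √0.20 = 0.246 SD, where 0.549 = 2.80 × √(2/52). This matches, for example, 3/12 for HbA1c and 5/20 for systolic pressure.

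2. **Loss from the change contrast.** Relative to an adjusted analysis: 1 - (1-rho²)/(2(1-rho)) = (1-rho)/2.

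| rho | 0.9 | 0.7 | 0.5 | 0.3 | 0.15 |
|---|---|---|---|---|---|
| loss | 5% | 15% | 25% | 35% | 42.5% |

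3. **Check on the planned five visits.** Generalised least squares with visits at 0, 4, 12, 18 and 24 months, compound symmetry, and terms t, t², log(t+1) (the offset of 1 is assumed). Replacing free intercepts by a common baseline mean cuts the variance of the 2-year change contrast by 44% at rho 0.15, 26% at 0.5 and 5% at 0.9. At 0.15 the cut ranges from 33% to 54% under reduced time forms. With a baseline correlation of 0.15 and follow-up visits correlated 0.6 (assumed), it is 42% for the full form and 19-25% for reduced forms.

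4. **What rho might be.** The protocol gives none for secondary outcomes. A rough value combines the Table 5 paired interval (n = 13) with the Table 2 SD: SD of change = half-width/2.179 × √13, then rho = 1 - SD of change²/(2 SD²).
   - HbA1c: 9.45/2.179 × 3.606 = 15.6; rho = 1 - 15.6²/(2 × 12²) = 0.15; loss 42.5%.
   - Systolic pressure: SD of change 25.7; rho 0.17; loss 41%.
   - Diastolic pressure: rho 0.75, loss 12.5%. Waist: 0.77, 11.5%. LDL: 0.78, 11%.
   - Uncertainty: the chi-square interval (12 df) on the HbA1c SD of change allows rho up to 0.56, where the loss is (1-0.56)/2 = 22%. For systolic pressure the upper limit is 0.57.
   - Warning sign: the same method gives -0.79 for HDL and about 0 for insulin dose and depression. The pilot and the Table 2 SDs do not fit together well.

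5. **Meaning at 52 per arm.** For HbA1c at rho 0.15, the difference detectable with 80% power is 12 × 0.549 × √1.70 = 8.6 mmol/mol on change and 12 × 0.549 × √0.9775 = 6.5 adjusted. At rho 0.5 the figures are 6.6 and 5.7. Where the adjusted analysis has 80% power, the change contrast has about 56% at rho 0.15 and 68% at 0.5.

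6. **What the elimination rule does.** With two visits, the arm difference in change correlates -√((1-rho)/2) with the arm difference at baseline. If the group term is kept only when the baseline difference is significant at 5%, the bivariate normal gives a false-positive rate for the change contrast in those trials of about 29% at rho 0.15 and 24% at 0.3, instead of 5%. The term would survive chiefly where the change contrast is most distorted by chance.

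**The case against.** The strongest reply is that the text does not say the group term stays. Under randomisation the baseline difference is non-significant about 95% of the time. Dropping the term while keeping the interactions gives exactly the common-baseline model. This stands against any claim that the models retain the term. It does not settle the matter, because the protocol does not say whether a main effect may go while its interactions remain, and a rule driven by the observed imbalance is not a prespecified adjustment.

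Second, no passage names the contrast for secondary outcomes; the change contrast is inferred from the sample size method and from the shared model. This also stands. But the obvious alternative, the 2-year group difference from the same free model, only moves the loss: about 2% at rho 0.15, 24% at 0.5 and 81% at 0.9 in the five-visit check.

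Third, a group-by-time mixed model is standard and valid, an article condenses, and the choice of contrast can be left to an analysis plan. That is fair for the contrast. The fixed effects and the reduction rule, however, are written out here.

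A reader might infer that the plan throws away 43% of the precision for HbA1c and blood pressure. The documents do not support that as a fixed figure. It assumes the group term is retained, takes an inferred contrast, and uses a point estimate from 13 patients at 4 months set against SDs whose source sample is not stated. It does not apply to diastolic pressure at all.

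**Conclusion.** The point holds as one of efficiency and prespecification, not of bias: under randomisation the change contrast is unbiased. Baseline adjustment is not specified for any outcome, and whether something equivalent results depends on data-driven elimination. If the group term is retained and the interactions carry the effect, the loss is about (1-rho)/2. The pilot suggests roughly 40% for HbA1c and systolic pressure, falling to about 22% at the upper limit of rho, and 11-13% for diastolic pressure, waist and LDL. For the primary outcome at the plan's own 0.90, adjustment moves power only from 81% to 83%, so the sample size is not in question. All secondary figures rest on pilot correlations that are rough and, for HDL, implausible. Nor would adjustment rescue the Table 2 target of 3 mmol/mol for HbA1c if the correlation is really low; at 0.15 even the adjusted analysis detects only about 6.5. The change should be made because it costs nothing, and with large samples it loses no precision at any correlation.

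**What to change.** In Statistical analyses, state for each outcome one of two forms:

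- **Common baseline mean:** no treatment-group term at the pre-randomisation visit, and treatment-time terms only after it.
- **Baseline covariate:** post-randomisation visits as outcomes, with the patient's own pre-randomisation value as a covariate.

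For secondary outcomes that value is the one taken before the diet. For weight it is the 8-week value, so the treatment-time terms for weight must start at 8 weeks. Name the contrast to be reported, and exempt the baseline term and all treatment terms from the Wald elimination. Correct the remark in Randomization that later adjustment is impossible.

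The cost is a few lines of text. No patients, visits or data are added.

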## Discussion

To our knowledge, this trial is the first randomized controlled trial to test the effects of an integrated multi-model cognitive group therapy in the battle against weight regain after a successful weight loss intervention (VLCD) in patients with type 2 diabetes. Weight regain is common in the obese population in general, but even more pronounced in the diabetes type 2 population, and with more devastating effects on their health outcomes. The strength of this study is the combined psychological intervention (CPI) of cognitive restructuring, problem solving treatment and proactive coping, which will provide powerful tools to the participants for maintaining behavioral change and improving health outcomes. We expect that adding CPI to a VLCD will be effective in maintaining weight loss, improving lifestyle and, as a result, leading to improved glycaemic control and a reduction of cardiovascular risk.

We expect that a number of factors may influence the treatment effect, therefore we will also examine potential determinants of weight maintenance, such as depression, anxiety, self-esteem, fatigue, somatic symptoms, eating disorders and lifestyle. Apart from being predictive for the success of the intervention, these factors may be changed by the treatment itself and therefore will be followed over time as secondary outcome measurements.

It is expected that if the intervention is successful, it will also be cost effective since the costs of group counselling are relatively low and the expected reduction of medication, prevention or delay of complications and a reduction of hospital admissions are considered major cost savings. If the therapy is indeed effective, a formal cost effectiveness analysis will be performed.

Few studies have implemented interventions to sustain weight loss for longer then 18 months. In this study, we opt for a follow-up period of 2 years, enabling predictions on long-term behavioral change and weight maintenance. During the follow-up period, participants will have relapse-prevention group meetings with increasing intervals to stabilize behaviour. It is known that the effect of an intervention reduces when the contact with the therapist stops, and one can therefore expect that the participants experience a relapse in their behaviour after the follow-up period. The last session op CPI will be at 1,5 years after randomization, leaving the participants 6 months ‘to themselves’. Obviously, our patients remain under supervision of the healthcare team after completion of the study and will be encouraged to continue their good habits. Nevertheless, after 5 years, we will try to repeat the assessment of the main outcome variables to determine the long-term effect.

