**Methods and design:**

In a randomised parallel group intervention study, 140 patients with type 2 diabetes and overweight (BMI>27 kg/m2) will be recruited from the outpatient department of the Erasmus Medical Centre.

After obtaining ≥5% of weight loss with a VLCD, participants will be randomly assigned to CPI or usual care for 10 weeks. CPI consists of cognitive behaviour therapy, problem solving therapy and proactive coping.

Primary outcome measure is weight change (kg).

Other outcome measures are Body Mass Index (BMI = weight (kg)/length (m)2), waist circumference (cm), systolic blood pressure (mmHg), HbA1c (mmol/mol), lipid levels (LDL, HDL, TG (mmol/l) and chol/HDL-ratio), antidiabetic agents and doses, cardiovascular risk profile (UKPDS), lifestyle and quality of life (EuroQol EQ-5D). Psychosocial parameters are also studied, as secondary outcomes as well as determinants for weight loss.

When successful, we want to conduct an analysis of the cost effectiveness of the intervention as compared to usual care.

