### Objectives

The primary objective of this study is to determine if an integrated multi-model cognitive group therapy, is more effective in preventing weight regain after a Very Low Calorie Diet compared to usual care.

The secondary objectives are to investigate whether an integrated multi-model cognitive group therapy following a VLCD has an effect on glycaemic control, cardiovascular risk profile, psychological variables and quality of life, and subsequently to determine which patient group benefits most of the intervention.

The tertiary objective is to determine whether the intervention is cost-effective.

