#### Primary outcome

The primary endpoint with respect to the efficacy of CPI is the differential course of weight (kg) between both study groups, measured at 8 weeks and at 2 years follow-up. Weight is measured to the nearest 0.1 kg, after removal of shoes using a Seca 888 compact digital flat scale.

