b. Physical activity is measured using the SQUASH (Short Questionnaire to Assess Health Enhancing Physical Activity) [58]. The SQUASH collects days per week, average time per day, and effort for physical activities such as commuting activities, leisure time and sport activities, household activities, and activities at work or school. Total minutes of activity are calculated for each question by multiplying frequency (days per week) by duration (minutes per day). Activity scores for separate questions are calculated by multiplying total minutes of activity by an intensity score (range 1–9). The total activity score is calculated by taking the sum of the activity scores for the separate questions.

6. Cost-effectiveness

a. Quality of life is measured by the EuroQol (EQ-5D) [59,60]. The EQ-5D is 5-item self report questionnaire on which participants report if they experience any problems in mobility, self-care, usual activities, pain and anxiety/depression. Each dimension has 3 levels: no problems, some problems and severe problems. The scores on the three dimensions can be combined into one co called ‘utility’ score, which represents the societal value of quality of life. The utility score has a range from 1.00 (the value of health without health problems) till 0.00 (the value of health problems as bad a death). This societal value of quality of life is used as input for so called Quality Adjusted Life Years (QALY) analysis, as the societal perspective is the preferred perspective in health economics. The EuroQol instrument contains also the EQ-VAS, a vertical visual analogue scale with the anchors best imaginable health (score of 100) and worst imaginable health (score of 0). This EQ-VAS represents the patient’s perspective of quality of life.

b. Costs are measured by the Trimbos/iMTA Questionnaire for Costs associated with Psychiatric Illness (TiC-P) [61]. The TiC-P measures direct medical costs due to healthcare utilization during the past four weeks. Also, it registers the indirect non-medical costs due to productivity loss during the past two weeks.

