### Limitations

This trial is explanatory in design in relation to the measures of process but pragmatic in terms of the comparison with usual care rather than a specified alternative group. We chose this design to enable analysis of an additional intervention on top of usual care in a population already receiving multiple interventions. The pragmatic approach and planned economic analysis aim to facilitate implementation of the intervention when successful, but this design does not identify the optimal psychological therapy.

If the intervention is successful, it cannot be ascertained which of the 3 therapies involved determined the success. However, each of the treatments has been studied separately and is more or less proven effective in achieving weight reduction and maintenance [20,26,28-32,34-36,40]. We expect that a diet with a combination of several forms of cognitive behaviour therapy together will have a greater impact than the individual factors.

Clearly the assumption is that the overlap of effects of the different types of interventions is negligible. This is not necessarily true. Hence, the present study is designed to study the effect of a combination therapy, but cannot identify the optimal combination of interventions.

Another limitation is the comparison to usual care only. One could argue that the participants in the intervention group may benefit from the attention they get, and not necessarily from the CPI. In our study design, it is impossible to distinguish between the effect of attention and the effect of the intervention itself. Our choice to compare our intervention on top of usual care with usual care only, is based on the fact that this kind of comparative effectiveness design has more clinical relevance. Such design is a necessary condition for a cost effectiveness analysis, as cost effectiveness is measured in relation to the dominant alternative treatment strategy. Moreover, the individual interventions have been shown effective in comparison with other psychological interventions, exercise or placebo as a control [27,35,40,65].

We are aware of the fact that our population is not generalizable to the entire group of overweight patients with type 2 diabetes.

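### Cost-effectiveness is an unconditional objective, but the formal analysis is to be run only if the therapy proves effective, a condition that is not defined

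*Protocol article*

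**What the plan says.** The Objectives section carries no condition: "The tertiary objective is to determine whether the intervention is cost-effective". Secondary outcomes has a cost-effectiveness item with two parts, EQ-5D and the TiC-P cost questionnaire. Of the EQ-5D utility it says "This societal value of quality of life is used as input for so called Quality Adjusted Life Years (QALY) analysis". Outcome assessment schedules the secondary outcomes at baseline, 4 months, 1 year, 1½ years and 2 years, and does not tie them to any result. Limitations treats the economic work as part of the design: "The pragmatic approach and planned economic analysis aim to facilitate implementation of the intervention when successful".

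Two other places make the analysis conditional. The Abstract (Methods and design) says "When successful, we want to conduct an analysis of the cost effectiveness of the intervention as compared to usual care". The Discussion says "If the therapy is indeed effective, a formal cost effectiveness analysis will be performed", shortly after stating "It is expected that if the intervention is successful, it will also be cost effective". The document defines neither successful nor effective. The nearest candidate is the primary outcome, the "differential course of weight (kg) between both study groups, measured at 8 weeks and at 2 years follow-up".

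**The concern.** A conditional analysis cannot meet an unconditional objective. Whether CPI is worth its cost depends on the joint difference in costs and QALYs, and a verdict on weight does not settle that. A programme of 17 group sessions with no weight benefit still has a cost. A programme with little weight benefit might still save medication or improve quality of life.

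The protocol's own Background describes that second case. Under Cognitive behaviour therapy it reports that psychotherapy in type 2 diabetes improved HbA1c and well-being without an apparent effect on weight. Under Very Low calorie diet it reports that patients who regained most of their weight often still needed less antidiabetic medication.

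Because the trigger is undefined, the decision to run the analysis would be taken with the results in view. The design also leans on this analysis: Limitations defends the usual-care comparator partly because a cost-effectiveness analysis requires it, and accepts five 30-minute questionnaire sessions as a burden, especially on controls.

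**Working it through.** **The texts side by side.** Objectives: unconditional. Secondary outcomes and Outcome assessment: cost and utility data collected without condition. Limitations: economic analysis planned. Abstract and Discussion: analysis only on success. No place says what economic analysis follows a negative or inconclusive result.

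**Inputs (Sample size calculation).** Mean weight 110 kg, SD 22 kg, baseline-end correlation 0.90, alpha 0.05 (taken as two-sided), power 0.80, target difference 5% of 110 = 5.5 kg, 52 per group, 25% dropout, 140 in total.

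**Reproducing the plan's figure.**
- SD of change = 22 × √(2 × (1 − 0.90)) = 9.84 kg.
- The normal approximation gives 51 per group. The noncentral t gives power 0.798 at 51 and 0.806 at 52, hence 52.
- 104 / 0.75 = 138.7, so 139, or 70 per arm = 140. The stated sample size reproduces and is not in dispute.

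**Chance that the analysis is not run.** Assumption: effective means a two-sided significant weight difference in favour of CPI, using the standard error implied by the plan's inputs.
- SE = 9.84 × √(2/52) = 1.93 kg.
- P(run) = Φ(δ/SE − 1.96).

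| True difference | δ/SE | P(run) | P(not run) |
|---|---|---|---|
| 5.5 kg (design) | 2.85 | 0.81 | about 20% |
| 2.75 kg (assumed, half the design value) | 1.425 | 0.30 | about 70% |
| 0 | 0 | 0.025 | 97.5% |

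**Selection when the analysis is run.** With θ = δ/SE, the expected upward shift of the weight estimate given significance, in SE units, is φ(1.96 − θ) / Φ(θ − 1.96).
- Nominal 80% power (θ = 2.80): 0.280 / 0.80 = 0.35 SE.
- 30% power (θ = 1.44): 1.16 SE.
- No effect (θ = 0): 0.0584 / 0.025 = 2.34 SE.

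If the weight and net-benefit estimates are jointly normal with correlation ρ, the net-benefit estimate shifts by ρ times that, in its own SE. The documents give no ρ, so a range of 0.1 to 0.5 is assumed.

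| Scenario | ρ = 0 | ρ = 0.1 | ρ = 0.5 |
|---|---|---|---|
| 80% power | 0 | 0.04 SE | 0.18 SE |
| 30% power | 0 | 0.12 SE | 0.58 SE |
| No effect | 0 | 0.23 SE | 1.17 SE |

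The largest shifts belong to scenarios in which the analysis would seldom be run.

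**The case against.** **The data would not be discarded.** EQ-5D and TiC-P costs sit under Secondary outcomes, and Statistical analyses applies a mixed model to each primary and secondary outcome without a condition. Quality of life is also an unconditional secondary objective. This stands: a reader might infer that a negative trial throws the economic data away, and the document does not support that. Only the formal synthesis is conditional. Separate comparisons of cost and quality of life do not, however, give the joint cost and QALY difference with its uncertainty, which is what the tertiary objective needs.

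**The trigger is inferred.** The document never says that the condition is a significant primary result, and the Discussion speaks of expected effects on weight, lifestyle, glycaemic control and cardiovascular risk. This stands too. The probabilities above hold only under the stated reading. That several readings are possible is itself part of the problem.

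**Bias toward CPI is not shown.** A reader might note that the weight estimate given significance is inflated by 0.35 × 1.93 = 0.68 kg at the design effect (12% of 5.5 kg), or by about 80% at 2.75 kg, and infer that the cost-effectiveness ratio would be equally over-optimistic. That does not follow, because kilograms do not enter a cost-utility analysis. The shift passes through only by way of ρ, and at ρ = 0 there is none. The Discussion presumes a positive link through less medication, fewer complications and fewer admissions, which gives a direction but no size.

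**It is an openly stated resourcing choice for a tertiary objective.** True, and it leaves randomisation, sample size and the primary inference untouched. It still conflicts with the objective as worded. Details such as a cost-effectiveness plane or acceptability curve may fairly be left to a fuller document; the condition itself is stated in this one.

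**Conclusion.** The inconsistency is certain from the text and rests on no calculation: the objective is unconditional, the analysis is conditional, and the condition is undefined. Reading the condition as a significant weight result puts the chance of an unanswered objective between about 20% (design effect) and 97.5% (no effect), with about 70% at the assumed 2.75 kg. The loss is the joint cost and QALY answer.

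Distortion when the analysis is run is a possibility, small at design power under the assumed correlations, and its size cannot be determined from the documents. The point deserves correction because the remedy is simple and the protocol's own Background shows that economic value need not follow weight. It does not threaten the primary result.

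**What to change.** Delete the condition in the Abstract and in the Discussion. State instead that the cost-utility analysis, giving the joint difference in costs and QALYs with its uncertainty in all randomised patients, will be done whatever the weight result. Intention-to-treat is already planned for all analyses, so this adds no new principle. If the condition is to stay, the second-best course is to word the tertiary objective as exploratory and conditional, and to define effective before results are seen.

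The sample size stays at 140 and no further data are needed. The cost is analyst time, some of which may go to an intervention that proves ineffective.
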